### *Power and participation*

We have estimated power on the outcomes: distress (distress thermometer), anxiety and depression (hospital anxiety and depression scale) based on results from the pilot study (N=50) (Figure 3) where we observed an up to 30% difference in change from case to non-case in the intervention versus the control group on distress and anxiety.

**Figure 3. Percentage of women changing from cases to non-cases in intervention and control group**

| Control group (%) | Intervention group (%) |
|-------------------|------------------------|
|-------------------|------------------------|

|                         |    |    |
|-------------------------|----|----|
| Distress ( $\geq 7$ )   | 61 | 90 |
| Anxiety ( $\geq 8$ )    | 53 | 80 |
| Depression ( $\geq 8$ ) | 44 | 49 |

Conservatively, we expect slightly lowered differences in change from case to non-case in the large full-scale study (20 %), compared to those observed in the pilot study (30%).

In a 2-year period, we expect 948 women to fulfill the inclusion criteria. With an expected participation rate of 80% (85% was reached in the pilot study) 758 will participate. Of these 43% will have high distress (N=324) and will enter the RCT. 57% will have low distress (n=432) and will be invited to participate in observation group who will fill-out questionnaires.

Due to a large number of planned analyses in the RCT study, we assume a highly conservative alpha to be 1%. Within a 2-year inclusion period, we will include 324 patients and an estimated 20% will drop-out or have missing data, resulting in final sample of 260.

With 130 women in each group, an expected 61% women move from cases to non-cases on distress in the control group and 81% percent women move from cases to non-cases on distress in the intervention group, we will obtain 84% power. Similar calculations for anxiety and depression reveals power of 78% and 76%.

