| Neuropathy         | Single items            | X                       |                  |                   |                   | X                  | X                   | X                   |

|                    |              |   |  |  |  |   |   |   |
|--------------------|--------------|---|--|--|--|---|---|---|
| Sleep              | PSQI         | X |  |  |  | X | X | X |
| Cognitive function | FACT-cog     | X |  |  |  | X | X | X |
| Health behavior    | Single items | X |  |  |  |   |   | X |
| Need for support   | Single items | X |  |  |  | X | X | X |
| Quality of life    | EQ-5D        | X |  |  |  |   |   | X |
| Acceptability      | Single items |   |  |  |  |   |   | X |

Note. MOS Medical Outcomes Study Social Support Survey (17). DT Distress thermometer (18,19). GAD 7 Generalized Anxiety Disorder (20). PHQ 9 (depression) The Patient Health Questionnaire (21). FACT-B Functional Assessment of Cancer Therapy –Breast (22). Physical Function Scale (29). PAM Patient Activation Measure (23). CARQ Fear of Recurrence (24). Pain (single items), neuropathy (single items). PSQI Pittsburgh Sleep Quality Index (25). FACT-cog Functional Assessment of Cancer Therapy-Cognitive (26). Health behavior including smoking, alcohol, physical activity, BMI (single items). Need for support (single items). EQ-5D Euro Quality of Life-5-Dimensional Classification (27).

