## STATISTICAL ANALYSES

Descriptive analyses will provide information on inclusion, feasibility, including participation in intervention components and data collection, satisfaction with the intervention, and information on nurse management of symptoms from medical records. Analyses will be based on intention-to-treat, with t tests to compare mean differences in change in each group between baseline and 6, 12 and 18 months of follow-up and with mixed models including all follow-ups. Primary analyses will test the effect of the intervention on distress, and secondary analyses will test for psychological symptoms, physical symptoms, and health behaviour (smoking, alcohol, BMI, physical activity). The effect of the intervention in the control and the intervention group will be assumed to be normally distributed and will be tested by the F-test. In all analyses, 99% confidence intervals will be calculated. Analyses will be performed based on the intention to treat principle including all participants and in sensitivity analyses, imputations of missing data will be performed using the last-observation-carried-forward method (28). In analyses aiming to describe the clinical impact of the intervention, we will estimate how many percent of the cases of distress, anxiety, depression and physical symptoms in the intervention versus the control group will be moved to non-cases. Furthermore, in cost-utility analyses, we will apply quality adjusted life years (QALY) to weigh the life expectancy of a patient against the Euro Quality of Life 5-Dimensions Classification (5Q-5D). Using incremental analyses, mean differences in costs (health care +disability + productivity loss + intervention) are compared with mean differences in health consequences for the intervention versus the control group.

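### The 78% and 76% power stated for anxiety and depression is arithmetically reproducible but not supported by the protocol's own inputs

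*Protocol*

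**What the plan says.** The Power and participation section says that power was estimated for distress and for "anxiety and depression (hospital anxiety and depression scale) based on results from the pilot study", a pilot of 50 women. It reports a pilot difference of up to 30% for distress and anxiety, and does not claim that figure for depression. Figure 3 gives the pilot percentages moving from case to non-case, control then intervention: distress 61 and 90, anxiety 53 and 80. The depression row reads "Depression ( $\geq 8$ ) | 44 | 49".

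The planning assumption follows: "Conservatively, we expect slightly lowered differences in change from case to non-case in the large full-scale study (20 %), compared to those observed" in the pilot (30%). On the error rate, "we assume a highly conservative alpha to be 1" per cent. The worked case is distress: "With 130 women in each group, an expected 61% women move from cases to non-cases on distress in the control group", against 81% in the intervention group, for 84% power. Anxiety and depression then get one sentence: "Similar calculations for anxiety and depression reveals power of 78% and 76" per cent.

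Three other places bear on this:

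- Participants and Randomization admit women to the trial on a distress thermometer score of 7 or more. Neither sets an anxiety or depression threshold.
- Statistical analyses defines the clinical-impact measure as the percentage of cases of each outcome that become non-cases. The tests themselves are t tests on mean change and mixed models.
- Figure 2 and its note list the instruments as "GAD 7 Generalized Anxiety Disorder (20). PHQ 9 (depression) The Patient Health Questionnaire (21"). HADS is not among them.

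**The concern.** A power figure is a claim about a particular comparison, in a particular number of women, on a particular measure. For anxiety and depression the protocol's own text disagrees with the claim on three counts: how many women can contribute to a case to non-case comparison, which instrument defines a case, and (for depression) how the assumed effect relates to the pilot result it is said to be based on.

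The protocol chose to publish these figures, and Paper 1 in its dissemination plan reports anxiety and depression beside distress. Readers of that paper would take 78% and 76% as the sensitivity of the case to non-case comparisons. The design does not deliver those powers on its own definitions.

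**Working it through.** **Inputs.** 130 evaluable women per arm (324 × 0.8 = 259.2, rounded to 260); alpha 1%; control rates 61%, 53% and 44% from Figure 3; assumed gain 20 points. Sidedness is not stated. Two-sided is assumed, which agrees with "In all analyses, 99% confidence intervals will be calculated".

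**Formula.** Two-proportion z test with pooled variance under the null:

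- p̄ = (p1 + p2)/2
- SE0 = √[2p̄(1 − p̄)/n]
- SE1 = √[(p1(1 − p1) + p2(1 − p2))/n]
- power = Φ[(|p2 − p1| − 2.576 × SE0)/SE1]

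**Step 1: reproduce the stated figures (n = 130 per arm).**

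- Distress, 61 v 81: (0.20 − 2.576 × 0.0563)/0.0549 = 1.00, power 84.2% (stated 84).
- Anxiety, 53 v 73: (0.20 − 2.576 × 0.0599)/0.0586 = 0.78, power 78.3% (stated 78).
- Depression, 44 v 64: (0.20 − 2.576 × 0.0618)/0.0606 = 0.67, power 75.0% (stated 76; unpooled variance gives 76.6%).

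The calculation therefore added 20 points to each pilot control rate and counted every evaluable woman as a case. A one-sided 1% test (89.6, 85.0, 82.3%) and a continuity correction (80.6, 74.2, 70.8%) both fit worse.

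**Step 2: the denominator.** For distress, the entry criterion is also the case definition, so 130 is right. For anxiety and depression, 130 is right only if every randomised woman is also a baseline case of each. The protocol gives no baseline case share, so the rows below 100% are assumptions. They keep the 20-point gain and apply the same share to both arms.

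| Assumed case share | Cases per arm | Anxiety, 53 v 73 | Depression, 44 v 64 |
|---|---|---|---|
| 100% | 130 | 78.3% | 75.0% |
| 80% | 104 | 66.3% | 62.7% |
| 60% | 78 | 50.5% | 47.2% |
| 50% | 65 | 41.3% | 38.4% |
| 30% | 39 | 22.3% | 20.6% |

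**Step 3: the effect size.** Pilot gaps from Figure 3:

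- distress 90 − 61 = 29 points
- anxiety 80 − 53 = 27 points
- depression 49 − 44 = 5 points

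Twenty points is a reduction for the first two and four times the observed gap for the third. At 44 v 49 with 130 per arm: (0.05 − 2.576 × 0.0619)/0.0618 = −1.77, power 3.8%. At that difference, 76% power would need about 2,143 cases per arm.

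**Step 4: the instrument.** The control rates of 53% and 44% are for HADS cases (cut-off 8). The trial will define cases on GAD-7 and PHQ-9. The protocol does not say why the rates should carry over. The effect on power cannot be computed from the document.

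**Step 5: what 130 per arm delivers on mean change.** Detectable difference = (2.576 + 0.994) × √(2/130) = 3.570 × 0.1240 = 0.44 SD, at two-sided 1% with 84% power, in all evaluable women.

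**The case against.** The strongest reply is that nothing was miscalculated: given 20 points and 130 per arm, the figures come out. That stands. A reader might infer an arithmetic error, and the document does not support that; the fault is in the inputs.

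Second, a reader might infer that the trial has almost no chance of finding an effect on depression. The protocol does not support that either. Its tests compare mean change in all participants by intention to treat, and case to non-case appears as a description of clinical impact. The 4% and the reduced-n powers apply to the dichotomised comparison only. The protocol gives no pilot mean difference for depression, so power on the mean scale cannot be judged against the pilot.

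Third, the 5-point gap is itself imprecise. Assuming 25 pilot women per arm, all of them cases, its standard error is √(0.4963/25) = 0.141. That gives a 95% interval of about −23 to +33 points, which includes 20. So 5 points is not established as the true effect, and power may properly be set on a justified target difference. What remains is that the protocol offers no such justification and instead calls 20 points conservative against the pilot.

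Fourth, the effect-size point does not reach anxiety, where 20 is below the pilot's 27. Planning from a related instrument is also not wrong in itself; the gap is that the transfer goes unaddressed. Both replies are accepted.

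**Conclusion.** The 78% and 76% are not supported as stated. Both require every evaluable woman to be a baseline anxiety case and a baseline depression case, which the entry criterion does not ensure. Both borrow case rates from an instrument the trial does not collect. For depression, the assumed gain also contradicts the protocol's description of it as conservative.

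The size of the denominator shortfall depends on a case share the document does not give: at an assumed 80% to 50%, power is about 66% to 41% for anxiety and 63% to 38% for depression. The 4% for depression needs no assumed case share, but it holds only for the case to non-case comparison at the pilot's own rates, with 130 per arm and two-sided 1%.

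It might be inferred that the whole sample size is unsound. It is not on these grounds: the 84% for distress reproduces, its denominator is correct, and anxiety and depression are secondary outcomes. The point should be corrected, but it does not threaten the primary analysis.

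**What to change.** Withdraw or restate the 78% and 76%. State in Power and participation that anxiety and depression are secondary outcomes measured by GAD-7 and PHQ-9, and give the difference that 130 per arm can detect on the mean-change comparison in Statistical analyses: about 0.44 SD at two-sided 1% with 84% power.

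If a case to non-case power is kept:

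- compute it on the expected number of GAD-7 and PHQ-9 baseline cases, with the source or assumption for that number stated;
- for depression, drop the description of 20 points as conservative, and either justify the target difference or show power over a range that includes the pilot's 5 points.

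The cost is protocol wording. Sample size, conduct and the primary analysis do not change. The drawback is that the stated power for these two outcomes becomes less favourable.

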## ORGANIZATION

[name], Professor, Ph.D., DMSc will be the principle investigator of the project. The daily project coordinator will be [name], Nurse specialist, R.N. and [name], Senior Researcher, Psychologist, Ph.D. will be research coordinator. The project will be followed by an advisory board including clinicians and researchers with great expertise in breast cancer patients.

The main project group includes:

- The Danish Cancer Society Research Center
  - [name], [name]
- Section of Breast Surgery, Rigshospitalet
  - [name], [name],

Further, the study advisory board includes:

- Oncology Clinic, Rigshospitalet
  - [name], [name]
- Oncology Clinic, Herlev Hospital
  - [name]
- Copenhagen Centre for Cancer and Health
  - [name]
- The Danish Cancer Society Research Center
  - [name]
- Section for surgical pathophysiology, Rigshospitalet
  - [name]

The project will start in April 2017, inclusion will end in April 2019, follow-up will end in October 2021 and analyses will end in October 2023.

## **ETHICS**

The study will follow ethical procedures for health research in Denmark, which is in accordance with recommendations from the National Board of Data Protection, ethical standards as outlined by the The Capital Region of Denmark's Ethical Committee ensuring voluntary participation and the right to best treatment available, irrespective of study participation. We will apply the Capital Region of Denmark's Board of Data Protection for permission. The study will also follow recommendations by the Helsinki-declaration II, the SPIRIT and CONSORT for randomized controlled trials of non-pharmacological treatment. The RCT will be made public, including the protocols at ClinicalTrials.gov before inclusion of the first participant.

Participation will be voluntary. Patients will receive written and verbal information about the study and will have 24 hours consideration period before signing informed consent form. Participants have the right to withdraw from the study at any time without giving any reason and withdrawal has no consequences for the participants continued treatment. We will collect information from national registries and from medical records and for this purpose we will obtain informed consent according to the Danish Health Legislation paragraph 43.1.

Participants in the REBECCA study will not be restricted from any activities or treatments outside the study. Inclusion in the study in either the intervention or the control arm does not involve any known side-effects, risks or harm. Further to ensure that participants will experience as few inconveniences as possible related to filling out the questionnaires we will use validate scales, which have already been tested on larger populations. We cannot rule out that the intervention may lead to increased risk for uncertainty and anxiety. All participants in the study are instructed to report if they experience any side effects, risks or harms associated with study participation. The participants in this study are covered by "The Danish Patient Insurance" although some of the trial investigators are not employed at a hospital.

There are no known circumstances that may lead to disruption of this study or that participants will be excluded from study participation. If this, contrary to expectations should be the case, participants will be informed about the reason for this. Participants who no longer fulfill the inclusion criteria, will not be excluded from the study. Patients will only be excluded from the study if they at any time do not wish to participate.

Data collected for this study will be securely stored according to the requirements from The Danish Data Protection Board at The Danish Cancer Society Research Center and at Section of Breast Surgery, Rigshospitalet. Permission for data storage is obtained from Region Hovedstaden.

## **DISEMINATION**

The results of the study will be disseminated through at least four scientific peer-reviewed publications. Further, a short Danish report will be developed summarizing the results and the clinical implications. We wish to ensure that knowledge from the project reach as far as possible to health professionals at hospitals, municipalities and private organizations

offering volunteer support. Results from the project will be presented at the yearly Danish breast cancer workshop targeting all nurses and medical doctors in Denmark and at two international conferences. Finally, a seminar will be arranged to present and discuss the results of the study. Here, we will invite health professionals in Denmark working with cancer rehabilitation, politicians and administrators from the health area as well as patients and relatives.

Working titles of peer-reviewed publications

Paper 1 RCT on the effect of individually tailored nurse navigation for distressed breast cancer patients on distress, anxiety and depression

Paper 2 RCT on the effect of individually tailored nurse navigation for distressed breast cancer patients on secondary outcomes of physical symptoms

Paper 3 The mechanisms at play in nurse navigation

Paper 4 The price for nurse navigation: Evaluation of an RCT comparing the cost of nurse-navigation and standard care

## **PERSPECTIVES**

The screening procedure proposed for eligibility is very simple and includes the single-item distress thermometer. It is expected that this will provide optimal acceptability from health professionals and could be implemented in clinical cancer settings with few barriers. The screening procedure applied at four time points is also developed to be as simple as possible. FACT-B and the distress thermometer. Still, implementation of the intervention into clinical practice will demand nurse resources to manage the screening procedure and the symptoms identified. This underlines the importance of our planned evaluation of implementation cost and cost-effectiveness as part of the study design as this will inform hospitals in Denmark of the pros and cons of the intervention.

If the REBECCA intervention shows positive effects on psychological and physical symptoms both in terms of statistical and clinical significance and if the cost-effectiveness is promising, we will contact all breast cancer hospital departments and hospital owners in the Danish regions to offer support on any implementation processes e.g. by providing the nurse navigation manual and training in its use.

## **FUNDING**

The Tryg Foundation has supported this project. The investigators are independent of Trygfonden and Trygfonden will have no influence on the research process or interpretation of results. The funding will be distributed equally during the five-year study period and the funders are responsible for the current audit of each their account. Salary to the project staff will be covered from these accounts. No financial reimbursement will be given to BC patients for participation in this study.

